### Qualitative study

The first part of the qualitative study focuses on patients’ experiences of care, aiming to better understand the specificity of patients’ perceptions of PC between outpatient consultation and day hospital. We will explored dimensions of organisation and process of care that contribute to satisfaction among patients received either PC models. This study is to take place in only one participating centre (Institute Curie), as heterogeneity across cancer centres is unlikely. Approximately 10 to 15 patients randomly selected from each intervention group will be interviewed 2 months after their inclusion by a research psychologist on their experiences and satisfaction with the palliative care provided. The recorded interviews will be transcribed and a qualitative analysis will be carried out using grounded theory constant comparison techniques [48, 49]. The semi-structured interviews will elicit patients’ care experiences with care providers and factors associated with PC, focusing on their perceptions of the medical and nursing care relationship: listening and support, the information and advice provided, the logistic aspects and continuity of care, the attention given to their loved ones and the impact of the care delivered. It will also explore their coping patterns and the role that PC could play in their psychological adjustment. Patients will be invited to talk about critical episodes or on the contrary particularly positive care experiences, and to provide any comments deemed useful to improve care.

The second part of the qualitative study focuses on PC health professionals in day hospital settings in order to understand organizational and professional aspect of PCDH work. To avoid a bias caused by specific features of one particular PC team, this survey will take place in two of the 5 participating cancer centres. Interviews will be conducted by two research sociologists, with PC physicians and nurses, and will concern the care of one or two patients randomly selected among patients seen the previous week, every week for 5 to 6 months. Research continues in cumulative mode until saturation is obtained, using grounded theory constant comparison techniques [48, 49]. Thus, an interactionist sociological survey will be undertaken concerning medical work in the PDCH (20). Data will be collected to reconstitute patient history, and questions will then focus on the description of the patients’ needs for supportive care, the PC discussions that took place, shared medical decisions, and the PC team’s feelings concerning the quality of care and relationships with the patients and their relatives.

### Medico-economic study

The study will be carried out from a societal point of view. A cost estimate will be made by collecting actual care consumption from the patients’ files for the last 3 months of life and assumptions will be made to estimate costs between inclusion in the study and the last 3 months of life.

Only costs that discriminate between the two strategies will be taken into account. Direct medical costs are costs directly attributable to the pathology and/or its treatment: care and medical and social expenditure.

These costs will include:

- Consultations carried out by community health (source of price data: fees established in General classification system for the professional activities, NGAP);

- Expensive medical and technical procedures such as MRI, or scanners (source of price data: fees established in the Common Classification of Medical Acts, CCAM);

- Hospitalization at home (source of price data: National average DRG related stay cost, ENCC 2016);

- The professionals’ interventions from the palliative care network or the mobile palliative care team (source of price data: bundled payment received by Hospital for public missions, MIGAC);

- Hospitalization in health care institutions, including rehabilitation units, acute medical care, etc. (source of price data: bundled payment received by Hospital for public missions, MIGAC);

- Care in day hospitalization (source of price data: National Cost Study 2016);

- Consultations in medical emergencies (source: of price data National average DRG related stay cost, ENCC 2016);

- Consumption of chemotherapy or other anti-cancer treatment (source of price data: Drug tariff database, BDM-IT);

- Medical transport expenses (source of price data: tariff established by the National Health insurance; the use of non-medicalized and non-healthy transport will be valued according to the rate per kilometer of transport and the distances travelled per kilometer).

A cost-effectiveness analysis will be conducted using the Global Survival effectiveness criteria.

The scores from the validated, specific HRQoL questionnaire EORTC QLQ-C30, will be converted into a score for the EuroQol 5 Dimensions questionnaire (EQ. 5D) [50] for inclusion in a cost-utility analysis. Another analysis will be carried out using a questionnaire that measures well-being according to the capability approach, the ICECAP-SCM [44]. This questionnaire has not yet been translated and validated in French. Therefore, this study will also contribute to the validation of this necessary tool for conducting medical and economic evaluations in the field of palliative care.

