### Endpoints

The primary outcome is deterioration-free survival (QFS) in PCDH with a three dimensions of the European Organization for Research and Treatment of Cancer Quality of Life Questionnaire Core30 (EORTC QLQ-C30) questionnaire targeted as co-primary endpoints: global health status, fatigue, and emotional functioning.

Secondary endpoints are the following:
Aggressiveness of EOL care according to usual criteria: in the last months before death, emergency consultations or hospitalizations, intensive care unit admissions, levels of anticancer treatment, place of death and length of stay in PC unit,Satisfaction with care according to the EORTC Out-Patient Satisfaction Core 33questionnaire (PATSAT-C33) and Out-patient satisfaction 7 (OUT-PATSAT7) questionnaires,Depressive and anxiety symptoms according to the Hospital Anxiety Depression Scale questionnaire (HADS),Patient awareness of negative prognosis according to the Prognosis and Treatment Perception Questionnaire (PTPQ),Advanced care planning,Needs for supportive care on the part of relatives according to the Supportive Care Needs Survey for Partners and Caregivers questionnaire (SCNS32-P&C-F),Overall survival,Direct costs of care (hospitalizations, consultations, home hospitalization, networks, anti-cancer treatments).

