**Patient**								
EORTC QLQ- C30	X	X	X	X	X	X	X	
PATSAT-C33 OUTPATSAT7					X		X	
PTPQ	X			X			X	
HADS	X			X			X	
ICECAP-SCM	X		X		X		X	
Medical-economic data assessment	X	X	X	X	X	X	X	X
End-of-life data collectionª		X	X	X	X	X	X	X

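### Costs before the last 3 months of life are to be assumed although economic data are scheduled at every visit, so the cost ratios rest partly or largely on assumed intervention-period costs; the societal label is also wider than the listed costs

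*Protocol article*

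**What the plan says.** The Medico-economic study section describes two sources for the cost estimate. One is "collecting actual care consumption from the patients’ files for the last 3 months of life". For the time before that window, "assumptions will be made to estimate costs between inclusion in the study and the last 3 months of life". The article does not describe these assumptions.

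Table 2 (Schedule of events) has a row "Medical-economic data assessment", marked at V1 to V7 and in the follow-up period, which is every column. It does not say what is recorded.

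On effects, the same section states: "A cost-effectiveness analysis will be conducted using the Global Survival effectiveness criteria". A cost-utility analysis uses QLQ-C30 scores converted to EQ-5D; Table 2 schedules the QLQ-C30 from V1 to V7. Under Statistical analysis, overall survival runs from randomisation.

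On perspective: "The study will be carried out from a societal point of view". The definition that follows is "Direct medical costs are costs directly attributable to the pathology and/or its treatment: care and medical and social expenditure", limited by the rule "Only costs that discriminate between the two strategies will be taken into account". The listed items are care, procedures, hospital and home hospital stays, day hospital, emergency visits, anti-cancer drugs and transport. The Endpoints section names the outcome "Direct costs of care (hospitalizations, consultations, home hospitalization, networks, anti-cancer treatments)".

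The Objectives section states the cost objective separately, as a lower cost of care in the 3 months before death.

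**The concern.** The ratios compare what each organisation of care costs with what it gains, and the gains are counted from entry. The experimental intervention also starts at entry and lasts 6 months. A cost window anchored backwards from death therefore leaves out the early intervention months of anyone who lives beyond 3 months, and those months are filled by assumption.

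Actual use in those months is hard to assume well. Under Procedure, experimental patients with no indication for day-hospital admission have an outpatient consultation instead, supportive care is given as needed in either arm, and hospitalisation can occur in both. The number of day-hospital stays, and any use they replace, will vary by patient. That difference between arms is what the economic study is meant to measure. The window is also set by death, which is itself an outcome: if survival differs between arms, so does the share of cost that is assumed.

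Separately, a reader of the results would take a societal ratio to include informal care and lost productivity. Neither is listed.

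**Working it through.** The article gives no cost figure, so there is nothing to reproduce. The check is on time windows.

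**Inputs.** Observed cost window: last 3 months of life (Medico-economic study). Intervention: 6 months from inclusion, then 6 months of follow-up (Procedure). Estimated life expectancy at entry: more than 2 and fewer than 12 months (Eligibility criteria). Median survival: not given, so 3 to 10 months is assumed.

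**Step 1, by month of death.** For death at month L:
- assumed months = max(0, L − 3)
- intervention months = min(L, 6)
- assumed intervention months = min(max(0, L − 3), min(L, 6))

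| Death at month | Assumed months | Share of entry-to-death time | Intervention months | Of these assumed | Share of intervention |
|---|---|---|---|---|---|
| 3 or earlier | 0 | 0% | up to 3 | 0 | 0% |
| 4 | 1 | 1/4 = 25% | 4 | 1 | 25% |
| 6 | 3 | 3/6 = 50% | 6 | 3 | 50% |
| 8 | 5 | 5/8 = 63% | 6 | 5 | 83% |
| 9 | 6 | 6/9 = 67% | 6 | 6 | 100% |
| 12 | 9 | 9/12 = 75% | 6 | 6 | 100% |

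**Step 2, over the whole sample.** With exponential survival, the lack of memory gives E[assumed intervention time] = P(T > 3) × E[intervention time]. The overall share is therefore P(T > 3) = 0.5^(3/m) for median m:
- m = 3: 0.5^1 = 50%
- m = 4: 0.5^0.75 = 59%
- m = 6: 0.5^0.5 = 71%
- m = 8: 0.5^0.375 = 77%
- m = 10: 0.5^0.3 = 81%

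A simulation of one million survival times per median agreed to within rounding. These are shares of time, not of money.

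**Step 3, patients alive at the end.** They have no last 3 months of life to observe. At 12 months the expected share alive is 0.5^(12/m): 6% for m = 3, 25% for m = 6, 44% for m = 10. Table 2 runs follow-up to week 104, whereas Procedure implies 12 months. At 24 months and m = 6 the share is 0.5^(24/6) = 6%. The size of this group therefore depends on which end of follow-up applies.

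**Step 4, perspective.** Set against the societal claim, the list holds care items and transport. The mention of social expenditure and the per-kilometre valuation of non-medical transport go a little beyond medical care. Informal care time and lost productivity appear neither in the list nor in the named endpoint.

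**The case against.** The strongest reply has five parts.

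- *The stated objective is served.* The Objectives section asks about cost in the 3 months before death, and the observed window matches it. This stands for patients who die. It does not cover the ratios.
- *Day-hospital care is observed.* It is a costed item, and stays in the last 3 months come from patients' files. This stands. A reader might infer that the ratios will not reflect observed day-hospital costs at all; the article does not support that. They are fully observed for deaths by month 3 and partly for deaths between months 3 and 9.
- *The schedule and the text may be compatible.* Table 2 does not say what the assessment records, and the assumptions could be built on those data. This stands as a caveat: that full consumption is collected at every visit is a reasonable reading, not a statement. The article still leaves the two places unreconciled.
- *The content of the assumptions belongs in the full protocol.* True, and their absence here is not the point. The point is the stated choice to assume rather than observe. A reader might also infer that cost uncertainty will be understated; the article says nothing on cost uncertainty, so that does not follow.
- *Only discriminating costs are counted.* This could justify leaving out informal care if it were not expected to differ. The article makes no such argument, lists relief of caregiver burden as an objective, and presents the day hospital as promoting home stay. A reader might go further and infer that work shifted to relatives would show as a saving; nothing in the text indicates such a shift.

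It is also fair to say that costs and effects both nominally run from entry. What differs is the source of the cost data for part of that period.

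**Conclusion.** The point holds for the cost-effectiveness and cost-utility ratios. Followed as written, they rest on assumed costs for a share of the intervention period that grows from 0% (death by month 3) through 50% (month 6) to 100% (month 9 or later). Overall this is about 50% to 81% of intervention time, given exponential survival with an assumed median of 3 to 10 months. The per-patient shares need no survival assumption; the overall range does. The window is undefined for patients alive at the end of follow-up.

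The cost in the 3 months before death is unaffected among patients who die, and the primary endpoint is not involved. The societal label claims more than the listed costs support, which is mainly a matter of labelling. This is a change that should be made, in a secondary analysis.

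**What to change.** Reconcile Table 2 with the Medico-economic study section:

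- Cost each patient from randomisation to death or the end of follow-up, using the consumption recorded at the scheduled assessments and in patients' files. State which end of follow-up applies.
- Limit assumptions to items that are not recorded, list them, and vary them in sensitivity analysis.
- Keep the last-3-months cost as a separate analysis in patients who died, answering the stated objective.
- Replace the societal label with one that matches the list, such as health-care costs plus transport.

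The cost is revised wording, more costing work and a narrower stated perspective. No new visits are needed if the scheduled assessments record consumption. If they record only part of it, more has to be taken from patients' files or left to declared assumptions.

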**Methods/design:**

This study is a multicentre parallel group trial with stratified randomization. Patient management in PCDH will be compared to conventional outpatient palliative care. The inclusion criteria are advanced cancer patients referred to a palliative care team with an estimated life expectancy of more than 2 months and less than 1 year. The primary endpoint is health-related quality of life with deterioration-free survival based on the EORTC QLQ-C30 questionnaire. The secondary objectives are the following: increase in patient satisfaction with care using the EORTC PATSAT-C33 and OUT-PATSAT7 questionnaires, better understanding of the prognosis using the PTPQ questionnaire and advance care planning; decrease in the need for supportive care among relatives using the SCNS-P&C-F questionnaire, and reduction in end-of-life care aggressiveness. Patients will complete one to five questionnaires on a tablet before each monthly visit over 6 months and will be followed for 1 year. A qualitative study will take place, aiming to understand the specificity of palliative care management in PCDH. Cost-effectiveness, cost-utility and, an additional economic evaluation based on capability approach will be conducted from a societal point of view***.***

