QFS will be estimated according to the Kaplan-Meier method and described per group using the median and confidence interval at (100-α) %. The comparison between the two RCT groups will be performed using log-rank test. A univariate Cox model will be performed to estimate the Hazard Ratio coefficient and its confidence interval at (100-α) %. Multivariate Cox models will also be conducted to explore the factors influencing QFS. All clinical and socio-demographic variables collected at baseline will be tested in univariate analysis. Variables with a *p*-value < 0.20 will be eligible for the multivariate model. This model will consider the collinearity of the eligible variables and will be constructed according to the Peduzzi rule of one variable for 10 events. The group will be forced into the multivariate model. Overall survival is defined by the interval between the date of randomization and the occurrence of death whatever the cause. It will be estimated according to the Kaplan-Meier method and described per randomized groups using the median and 95% confidence interval, and compared between the two groups using the Log-rank test. A univariate Cox model will be performed to estimate the Hazard Ratio coefficient and its 95% confidence interval.

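### Costing is anchored on death although Table 2 schedules economic data for every patient, so cost and survival effect can rest on different patients and periods

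*Protocol article*

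**What the plan says.** The Medico-economic study section bases the cost estimate on "collecting actual care consumption from the patients’ files for the last 3 months of life", and adds that "assumptions will be made to estimate costs between inclusion in the study and the last 3 months of life". The Objectives section frames the cost aim in the same way, as cost in the 3 months before death.

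For the effect side, the same section states: "A cost-effectiveness analysis will be conducted using the Global Survival effectiveness criteria". The Statistical analysis section gives the time origin: "Overall survival is defined by the interval between the date of randomization and the occurrence of death whatever the cause". The cost-utility analysis takes its utilities from the QLQ-C30, which Table 2 schedules for all patients at V1 to V7.

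Two other places point away from a death-anchored cost:

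- Table 2 has a medical-economic assessment row marked at V1 to V7 and in the follow-up period, with no footnote. The row below it, "End-of-life data collectionª", does carry a footnote that limits it to patients to whom it applies.
- The Endpoints section lists direct costs of care without any window before death.

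The follow-up length is given in two ways. The abstract says that patients "will be followed for 1 year", and the Procedure section agrees (6 months of study plus 6 of follow-up). Table 2 runs the follow-up period from week 24 to week 104.

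**The concern.** Both parts of the costing rule need a date of death. A patient alive at the end of follow-up has no last 3 months of life, and so no end point for the assumed period before it. The article gives no rule for such a patient, yet that patient contributes fully to survival from randomisation.

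The second difficulty applies also to patients who die. Protocol visits are monthly over the first 24 weeks, and day-hospital care is one of the listed cost items. For anyone who lives well beyond 3 months, much or all of that use falls before the measured window. The cost of the intervention under test would then be partly assumed, although the schedule provides for recording economic data over the same weeks.

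At stake is the validity of the cost-effectiveness and cost-utility comparisons. Cost and effect may come from different patients and different spans of time. If survival differs between arms, a cost comparison limited to patients who died is selected on an event that occurs after randomisation.

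**Working it through.** **Plan's own figure.** The article gives no calculation for the economic analysis. Its one sample-size calculation (HR 0.5, two-sided alpha 0.0166, power 80%) reproduces at 88 events by Schoenfeld's formula and is not affected by this point. The total of 144 patients, 72 per arm, is taken from it.

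**Assumptions.** The article gives no overall-survival median. I assume exponential survival, no loss to follow-up, and medians m of 4, 6 or 9 months, all within the entry criterion of an estimated life expectancy between 2 and 12 months. 104 weeks is 104/4.345 = 23.9 months.

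**Step 1: patients with no cost defined by the rule.** Share alive at time T = 2^(−T/m), times 144.

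| Assumed median | Alive at 12 months | Alive at 104 weeks |
|---|---|---|
| 4 months | 2^(−3) = 12.5%, 18 patients | 2^(−5.98) = 1.6%, 2 patients |
| 6 months | 2^(−2) = 25%, 36 patients | 2^(−3.99) = 6.3%, 9 patients |
| 9 months | 2^(−1.33) = 39.7%, 57 patients | 2^(−2.66) = 15.8%, 23 patients |

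**Step 2: how much time is measured rather than assumed.** Let X be survival time. Measured share of person-time = E[min(X, 3); X ≤ T] / E[min(X, T)]. For m = 6 and T = 12, the hazard is ln 2/6 = 0.1155 per month. The numerator is (1 − 2^(−0.5))/0.1155 − 3 × 0.25 = 1.79 months and the denominator is (1 − 0.25)/0.1155 = 6.49 months, so the share is 27.5%.

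- 12 months: 39%, 27.5% and 19% for medians of 4, 6 and 9 months.
- 104 weeks: 40.5%, 29% and 20%.

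Longer follow-up removes most of the survivors, but hardly changes the share of time costed by assumption.

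**Step 3: where the scheduled visits fall.** Take a death 9 months after inclusion, about 39 weeks. The measured window opens at about 39 − 13 = 26 weeks. V7 is due at 24 ± 2 weeks, so every scheduled visit falls in the assumed period.

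**Step 4: illustration if survival differs.** Assume a control median of 6 months and a survival HR of 0.8, so a PCDH median of 6/0.8 = 7.5 months.

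- Alive at 12 months: 72 × 0.25 = 18 control and 72 × 2^(−1.6) = 24 PCDH patients.
- Mean survival to 12 months, all patients: 6.49 against 7.25, a difference of 0.76 months.
- Mean survival among those who died by 12 months: (6.49 − 12 × 0.25)/0.75 = 4.66 against (7.25 − 12 × 0.330)/0.670 = 4.91, a difference of 0.26 months (from unrounded values).
- At 104 weeks: 4.5 against 7.9 of 72 alive, and differences of 1.52 months in all patients and 0.83 months in decedents.

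In this illustration the survival gain in all patients is about 3 times (12 months) or 1.8 times (104 weeks) the gain in the patients for whom the rule defines a cost.

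**The case against.** The strongest case on the other side has five parts.

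- **Data for survivors.** A reader might infer that survivors will have no cost data at all. The documents do not support that. Table 2 schedules medical-economic data for every patient, and the direct-cost endpoint has no death-anchored window. What stands is that the costing rule does not use those data and conflicts with the schedule.
- **Analysis set.** A reader might infer that the plan takes cost from decedents and effect from everyone. It names no patient set for either side of the ratio, and the Statistical analysis section promises intention-to-treat with all randomised patients. The mismatch is a consequence of following the costing rule, not a stated intention. An unseen analysis plan may well handle censored costs, but the death-anchored measurement is written into this article.
- **Follow-up.** One exclusion criterion concerns patients who cannot be followed until death, which suggests that follow-up to death was intended. At 104 weeks the number of survivors is small unless the median is long. This stands, and it is why both horizons are shown.
- **Survival difference.** The objectives claim no survival benefit, and the Background calls the effect of early palliative care on mortality uncertain. Selection on death therefore remains conditional, and the documents do not support saying that PCDH decedents will be enriched for rapid progression. The assumed pre-window costs do not depend on any survival difference.
- **End-of-life care.** A reader might extend the criticism to the aggressiveness endpoint, counted "in the last months before death, emergency consultations or hospitalizations, intensive care unit admissions". Restriction to patients who died is inherent in that endpoint. Replacing it with event rates from randomisation would answer another question, so its definition is not a fault.

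**Conclusion.** The concern holds for the economic comparison. The stated rule measures cost only in the last 3 months of life, assumes the rest, defines no cost for patients alive at the end of follow-up, and sits beside a schedule that provides for economic data on everyone. Followed as written, it gives a worse cost comparison than the scheduled data appear to allow.

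The number of patients affected ranges from 18 to 57 of 144 at 12 months and from 2 to 23 at 104 weeks, and the article does not settle which follow-up applies. At either horizon, between about 60% and 81% of person-time would be without measured cost. These figures rest on exponential survival, no loss to follow-up and assumed medians of 4 to 9 months; the arm-specific figures rest in addition on an assumed survival HR of 0.8.

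The primary endpoint and its sample size are untouched. This is a change that should be made to a secondary analysis, and it is not a reason to doubt the main comparison.

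**What to change.** 1. Reconcile the Objectives, Endpoints and Medico-economic study sections with Table 2, and state one follow-up length throughout.
2. For the cost-effectiveness and cost-utility comparisons, accumulate costs forward from randomisation in all randomised patients to one fixed horizon, using the medical-economic data that Table 2 schedules. Name a method for censored costs, such as a censoring-weighted mean, and restrict survival to the same horizon. For cost-utility, say how utilities are obtained after V7, the last scheduled QLQ-C30, or end the horizon there.
3. Keep cost in the last 3 months of life as a supportive analysis in decedents.
4. Keep the end-of-life aggressiveness endpoint as defined, report it as conditional on death, and give the number of decedents per arm.

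The cost is mainly wording, plus somewhat more analysis work. The last-3-month cost, now the stated cost objective, becomes supportive. Table 2 does not list what its medical-economic row records, so the sponsor should confirm that the listed cost items are captured there; if they are, no new data item is needed.

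### Inpatient stays are given a bundled public-mission payment as their price source, not a stay-level price, and the declared societal perspective does not match the direct costs listed

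*Protocol article*

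**What the plan says.** The Medico-economic study section of the protocol article lists each cost item with its price source. For inpatient care the entry is "Hospitalization in health care institutions, including rehabilitation units, acute medical care, etc. (source of price data: bundled payment received by Hospital for public missions, MIGAC". The entry directly above it, for professionals' interventions, reads "palliative care network or the mobile palliative care team (source of price data: bundled payment received by Hospital for public missions, MIGAC".

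Other hospital-type items have different sources. One entry is "Hospitalization at home (source of price data: National average DRG related stay cost, ENCC 2016", and emergency consultations use the same ENCC source. The setting of the experimental arm is priced as "Care in day hospitalization (source of price data: National Cost Study 2016".

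On perspective, the section opens with "The study will be carried out from a societal point of view", and the abstract says the same of the economic evaluations ("additional economic evaluation based on capability approach will be conducted from a societal point of view"). The only cost category then defined is direct medical cost: "Direct medical costs are costs directly attributable to the pathology and/or its treatment: care and medical and social expenditure". The Endpoints section names the cost outcome as "Direct costs of care (hospitalizations, consultations, home hospitalization, networks, anti-cancer treatments".

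**The concern.** There are two separate problems in the same section.

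**Price source.** To cost inpatient care, the number of stays or days in each arm must be multiplied by a price per stay or per day. The article describes the MIGAC source as a bundled sum paid to a hospital for public missions, and does not say how a unit value would be drawn from it. This is the item on which the economic argument leans most. The Background cites a Canadian study in which palliative care lowered end-of-life costs partly through fewer and shorter hospital and intensive-care stays. The Objectives include a lower cost of care in the 3 months before death. If inpatient stays are valued on a different footing from day-hospital sessions, the comparison of the two models of care is hard to interpret.

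**Perspective.** A societal result is normally read as including costs that fall outside the health-care system, such as unpaid care and lost work. If the analysis counts only direct care and transport, readers will credit it with a scope it does not have.

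**Working it through.** The article gives no unit costs, resource volumes or cost totals, so there is no figure to reproduce. The check sets the passages side by side.

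**Step 1: price sources in the Medico-economic study section**

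| Item | Stated source |
|---|---|
| Community consultations | NGAP fees |
| Costly imaging and technical procedures | CCAM fees |
| Home hospitalisation | ENCC 2016, DRG-related stay cost |
| Palliative network or mobile team | MIGAC, bundled payment |
| Inpatient stays (acute, rehabilitation) | MIGAC, bundled payment |
| Day hospital | National Cost Study 2016 |
| Emergency consultations | ENCC 2016, DRG-related stay cost |
| Anticancer drugs | BDM-IT tariff |
| Transport | National insurance tariff; per-kilometre rate for non-medical transport |

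Two of the nine items use MIGAC, on consecutive lines and with the same description of the source. Of the four hospital items (home hospitalisation, inpatient stays, day hospital, emergency), inpatient stays are the only one without a stay-level or cost-study source.

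**Step 2: what this does to the cost difference**

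Write the between-arm difference in mean cost as

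ΔC = Σ (n_k,PCDH − n_k,control) × p_k,

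where n_k is the mean use of item k per patient and p_k its unit price. For day hospital, p_k comes from a cost study. For inpatient stays, the stated source is a bundled payment, so p_k is not defined per stay or per day. The inpatient term therefore has no stated value, or only one that depends on an allocation rule the article does not give. With neither n_k nor p_k available, the size and sign of the error cannot be worked out.

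**Step 3: perspective against content**

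- Declared perspective: societal, in both the abstract and the Medico-economic study section.
- Category defined: direct medical costs.
- Items listed: nine, all care or transport.
- Endpoint: direct costs of care.
- Caregiver time, patient lost work and caregiver lost work: not listed.

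The section limits costs to those that differ between strategies. That rule does not clearly excuse leaving out caregiver costs, because alleviating caregiver burden is a stated secondary objective: the trial itself expects the arms to differ there.

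**The case against.** The strongest reply is that the article is a condensed account. The full protocol and its unit-cost tables are not shown, and a bundled amount can be turned into an average value per stay or per day. The matching wording on adjacent lines also looks more like a copying error than a considered choice. This much stands: a reader might infer that MIGAC does not vary with stays, that an avoided inpatient day would count for nothing, and that the comparison is therefore tilted against day-hospital care. The documents support none of these. They do not say how the payment behaves or how it would be converted. Keeping MIGAC for networks and mobile teams also presupposes that some value per intervention can be derived from it.

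On perspective, three things soften the point. The definition of direct costs includes social expenditure. Non-medical transport is valued by distance, which goes somewhat beyond a payer's view. The schedule of events has a medical-economic assessment at every visit and in follow-up, whose content the article does not describe. A reader might infer that no caregiver or productivity data are collected, but the article shows only that none are listed among the costs. The caregiver questionnaire does cover the effect of illness on work, though as a score of needs and not as a cost.

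The reply does not remove the two mismatches. Both are in what the article states, not in what it leaves out: it names a specific source for inpatient stays that does not fit the item, and it names a perspective wider than the costs it itemises.

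**Conclusion.** The point holds in limited form. As written, inpatient stays have no per-stay or per-day price source and would not be valued on a basis matching day-hospital sessions. The societal label is not supported by the listed costs. Both bear on the cost-effectiveness, cost-utility and capability-based results. They do not touch the primary endpoint, the sample size or the clinical secondary endpoints.

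No amount and no direction can be given. The conclusion assumes that the bundled payment is what the article's own description says it is, and that the nine listed items are the costs to be counted. That the inpatient source was duplicated from the line above is likely but not established. A correction or clarification is needed either way, and it should be made, since the Discussion relies on the economic study to assess the economic consequences of day-hospital care and foresees national guidelines if the trial's results are favourable.

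**What to change.** 1. **Inpatient stays.** State a stay-level or day-level national cost source for acute stays, for example the ENCC source already used for home hospitalisation and emergency visits. Name an equivalent stay- or day-level source for rehabilitation stays separately, because the documents do not show that ENCC covers them. Keep MIGAC for networks and mobile teams, and say how a value per intervention is obtained from it.
2. **Perspective.** In the abstract and the Medico-economic study section, replace the societal label with one that matches the costs counted: direct medical and transport costs. A plain payer label would not fit well, given the per-kilometre valuation of non-medical transport.

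The cost is one revised unit-cost table, changes of wording, and a narrower stated perspective. No new patient data are needed.
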